## Discussion

The continuing high malaria burden in many areas of Africa calls for improving the effectiveness of malaria intervention tools [1]. This will require optimizing current first-line interventions and integrating newly approved tools into control programs [100]. Due to the heterogeneity and dynamic changes in malaria risk and vector ecology among epidemiological settings, interventions that work in one setting may not work well in others. This trial study aims to develop adaptive intervention strategies tailored toward local malaria risks and vector ecologies based on the available set of interventions and cost factors at a point in time. Such an adaptive strategy is expected to enhance the efficiency of malaria interventions. If adaptive interventions built from modern data analytic methods work well, they could provide new malaria vector control strategies in Africa and other endemic areas where malaria incidence is high or has rebounded since the implementation of currently used intervention tools.

Randomized controlled trial (RCT) design has been used to evaluate malaria control interventions [28, 101–103]. The SMART design represents a significant departure from standard RCT design, in which the intervention method is fixed a priori. In contrast, in the SMART design, the intervention method is adaptive, i.e., data from the early response to an intervention and predicted future risks are used to determine the next intervention method for those enrolled in the trial. Adaptive intervention is necessary for several reasons. First, given the many available and emerging malaria vector control tools, finding the best intervention or combination of interventions is not easy. It would be very difficult if not impossible to design an RCT due to the potentially huge sample size needed. Second, due to the heterogeneity and dynamic nature of transmission, interventions must adapt and readapt to the changing epidemiology. Third, standard RCT does not allow interventions to be adjusted during the trial, whereas adaptive intervention allows for changes, making it easier to find the best-suited intervention. Therefore, results from the adaptive intervention provide evidence for effective interventions that are closely tailored to local malaria risks, vector ecologies, and intervention logistics. To our knowledge, this is the first cluster-randomized SMART for malaria.

Recent developments in predictive data analytic techniques and machine learning provide novel tools to assist in identifying mosquito larval habitats and assessing malaria risks [101, 102]. Machine learning, such as reinforcement learning, has been used to identify optimal intervention strategies in clinical treatment studies [80, 86–88]. Reinforcement learning techniques are being used increasingly in the area of personalized medicine [103, 104] but have not previously been used for malaria. We will use *Q*-learning to identify larval habitats and to find the optimal intervention suited to local malaria epidemiological settings. The trial will include larviciding using long-lasting larvicides and IRS with new insecticides. The combination of satellite image analysis and machine learning will aid significantly in locating mosquito breeding sites and implementing IRS.

### Trial status

This trial is underway. Pre-intervention epidemiological and entomological surveillances were started in July 2019. Cluster selection, stratification, and randomization have been done. Demographic surveillance has been conducted once, in July 2019. Cohort active case surveillance was initiated in October 2019 and officially started in March 2020. The stage 1 intervention started recruiting in late February 2020, and recruitment will continue until March 2021 as anticipated. Post-intervention follow-ups started in March 2020 till February 2022. The trial was registered with US National Institutes of Health at ClinicalTrials.gov, study ID NCT04182126. Registered on 26 November 2019 and last updated on 3 March 2020. The manuscript was prepared when the trial protocol was registered; trial protocol was submitted for publication when recruitment of study participant was ongoing.

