### Cluster stratification for interventions

For each cluster, we will determine vector abundance and malaria infection prevalence. Malaria risk in each cluster will be predicted based on the predictive features (variables) described above. We plan to adopt two approaches for risk prediction. The first approach (classification-based) will first stratify the study clusters into distinct strata based on weighted vector abundance and malaria infection prevalence using *k*-means or hierarchical clustering algorithms [75]. A classifier will be trained to predict risk-group assignments based on predictive variables. To avoid overfitting, we will first try classification models with low complexities, such as naïve Bayes, softmax, and support vector machines (SVM) to establish a baseline, and then move to more complex models, such as decision trees, random forests, and neural networks [76–81]. The second approach (regression-based) will directly predict prevalence and malaria transmission intensity based on the predictive variables using Gradient Boosting (GB) linear and logistic regression (LogitBoost) or an ensemble of regression trees [82]. Each method has pros and cons. The classification-based approach is easier to interpret and less prone to overfitting, but the cluster assignment may not be clear-cut. On the other hand, although it does not require cluster assignment, the regression-based approach must model prevalence and vector abundance separately and is thus more prone to overfitting with nonlinear models [83].

The data from all study clusters (36 initially) will be split into a training set and a validation set, with model parameters trained on the training set and performance evaluated on the validation set. Tenfold cross-validation will be performed to maximally utilize the data [84, 85]. For the classification task, we will determine each model’s sensitivity and specificity and use the auROC (area under ROC curve) to measure model performance. For the regression task, we will use the mean-square loss to measure model performance. Trained models will be further tested and refined on data from 36 different clusters collected in year 2 and future years.

The goal is to stratify all clusters into 3 blocks during the initial intervention stage: low transmission, intermediate transmission, and high transmission.

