#### Stage 1 intervention

Stage 1 (initial intervention) will be 15 months long, including a 3-month field implementation of interventions and 12 months of follow-up on the interventions’ impact. The main purpose of stage 1 is to determine the effect of the individual interventions on malaria incidence and to identify clusters not responding to these interventions. At the beginning of stage 1, all study clusters will be randomized with equal probability to the three interventions, as shown in Fig. 2, by a block randomization method. At the end of the 12-month follow-up, clusters will be assessed for “response” versus “non-response” to PBO Nets or LLIN + IRS. Response and non-response are defined based on the change in clinical malaria incidence when using PBO Nets/LLIN + IRS compared to LLIN (Fig. 2). If a cluster demonstrates a reduction in malaria incidence that is (1) statistically significant and (2) greater than the pre-defined threshold value set by the Ministry of Health (MoH) based on cost-effectiveness, then this cluster is considered a responder; otherwise, the cluster is considered a non-responder. It is important to use the LLIN group (group A in Fig. 1) as the comparison group when determining response/non-response, because malaria incidence varies between seasons and years due to seasonal or inter-annual climatic variability. In addition, LLIN is the government-implemented first-line routine intervention.

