### Data analysis

Differences in clinical malaria incidence and vector abundance between the treatment and control groups will be analyzed using Poisson multivariate regression models with intervention, malaria risk, cluster, and calendar time as covariates, using a generalized estimating equation (GEE) approach with population at each cluster as an offset [96]. GEE is necessary because incidence will be modeled monthly as a longitudinal measure using grouped data. Intervention will be a time-varying covariate, since the treatment in a cluster may be adapted and readapted depending on the response to the previous treatment. The odds ratio and 95% confidence interval for clinical malaria rates between the treatment groups and the control group will be calculated. For the second aim analysis (estimation of outcomes for the 4 embedded adaptive interventions), weighted and replicated generalized estimating equations will be used to estimate the mean clinical malaria incidence rates among the 4 embedded adaptive interventions and to compare the slopes at each stage for each adaptive intervention. Here, weighting is necessary to account for the potential over- or underrepresentation of some groups (e.g., non-responders would have a 1/4 chance of following their assigned treatment sequence, whereas responders would have a 1/2 chance of following their assigned treatment sequence) [97, 98].

We will identify a final intervention strategy after all cost and effectiveness data are collected. The aim of this strategy will be to recommend an optimal intervention method given the local conditions at each site. For this purpose, we will adopt the *Q*-learning framework from the previous section on enhanced machine learning methods [99]. We will train a neural network to predict each method’s utility, accounting for both effectiveness (reduction in malaria incidence rate) and cost based on the conditions at each site, such as malaria risk and socioeconomic, entomological, and genetic features. All data collected throughout this research will be used to train the final model. To reduce model complexity, we will consider clustering sites into a small number of classes and then training a model to predict the efficacy of each method conditioned on each class. Once the *Q*-function is learned, we will identify the optimal intervention by choosing the intervention method that maximizes the learned *Q*-function.

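### The stated model does not adjust for the clinical incidence recorded in each cluster before stage 1, which costs precision with 12 clusters per arm

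*Protocol article*

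**What the plan says.** All references are to the protocol article.

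- **Timing (Trial status).** "Pre-intervention epidemiological and entomological surveillances were started in July 2019". For the cohort that yields clinical incidence, "Cohort active case surveillance was initiated in October 2019 and officially started in March 2020". As to the intervention, "The stage 1 intervention started recruiting in late February 2020", and "Post-intervention follow-ups started in March 2020 till February 2022".
- **Use of baseline data.** Trial design describes a baseline period. Baseline surveys for cluster randomization says that the baseline data will also serve to evaluate the interventions. The surveys described in its subsections cover demography, vectors, infection prevalence and environmental predictors, but not clinical incidence.
- **Blocks (Cluster stratification for interventions).** In the classification approach, strata are formed "based on weighted vector abundance and malaria infection prevalence".
- **Model (Data analysis).** A Poisson GEE on monthly grouped counts "with intervention, malaria risk, cluster, and calendar time as covariates", with intervention time-varying.
- **Responder rule (Stage 1 intervention).** "Response and non-response are defined based on the change in clinical malaria incidence". The same sentence goes on to make this a comparison with LLIN, and the section explains that the LLIN group is needed because incidence varies by season and year. The rule for a single cluster then asks for a significant reduction above a threshold, without repeating the reference.

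**The concern.** A cluster's earlier incidence is a natural predictor of its later incidence, and the trial has been recording it since October 2019. The stated model makes no named use of it. The blocks capture it only indirectly, through vectors and prevalence. The article itself lists incidence rate among the cluster features for the Q-function (Enhanced machine learning method), so it is treated as informative there but not in the effectiveness model.

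With 12 clusters per arm, the arms can differ by chance in underlying incidence by as much as the smallest effect the trial is designed to detect. An unadjusted analysis carries that difference as noise.

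The covariate list also leaves the role of cluster open, as a fixed effect or as the GEE grouping unit. That choice decides how baseline incidence can enter at all.

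**Working it through.** **Step 1. Calendar.** The months before stage 1 with cohort surveillance are October 2019 to February 2020, which is 5 months. Study area and cluster selection puts the major vector peak in April to June and the minor one in October to November. The window therefore holds none of the 3 major-peak months and both minor-peak months.

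**Step 2. Expected baseline cases per cluster.** Inputs from Sample size justification: 302 cases per 1000 person-years and 500 people per cluster.
- Per year: 0.302 × 500 = 151.
- Five months, spread evenly: 151 × 5/12 = 63.
- Five months if April to July carry twice the rate of other months (an assumption; weights sum to 4 × 2 + 8 × 1 = 16): 151 × 5/16 = 47. This figure is used below.

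**Step 3. Between-cluster variation.** With ICC 0.05 (same section), CV² = 0.05 × 0.698/0.302 = 0.1156, so CV = 0.34. At ICC 0.02, CV² = 0.0462 and CV = 0.215. The article cites earlier studies with values below 0.02.

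**Step 4. Chance imbalance.** The SD of the difference between two arm means of the true log rate is approximately √(2 × 0.1156/12) = 0.139. The log of a 10% reduction is −0.105. So at ICC 0.05, before allowing for blocking, a one-SD imbalance exceeds the 10% effect in the power table. With an assumed CV after blocking of 0.2, it is √(2 × 0.04/12) = 0.082.

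**Step 5. Reliability of the baseline rate.** Reliability = CV²/(CV² + 1/cases).
- CV 0.34: 0.1156/(0.1156 + 1/47) = 0.845.
- CV 0.215: 0.0462/(0.0462 + 1/47) = 0.69.
- CV 0.2: 0.04/(0.04 + 1/47) = 0.65.

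**Step 6. Proportional fall in between-cluster variance** = r² × reliability, where r is the correlation of true baseline and follow-up cluster rates. The document does not give r, so a range is shown.

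| r (assumed) | CV 0.34 (ICC 0.05) | CV 0.215 (ICC 0.02) | CV 0.2 (assumed, after block) |
|---|---|---|---|
| 0.3 | 8% | 6% | 6% |
| 0.5 | 21% | 17% | 16% |
| 0.8 | 54% | 44% | 42% |

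**Step 7. Effect on the standard error.** For one year of follow-up, the SE of the log rate ratio between two arms is √(2 × (between-cluster variance + 1/151)/12). At CV 0.34 it is 0.143 unadjusted, and 0.137, 0.128 and 0.100 for r = 0.3, 0.5 and 0.8. The SE is therefore 4%, 11% and 30% smaller.

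**Step 8. How cluster enters the model.** After March 2020, stage 1 intervention does not change within a cluster. If cluster is a fixed effect and only stage 1 follow-up months are analysed, the intervention term is a linear combination of the cluster indicators and cannot be estimated. A baseline rate is likewise constant within cluster and aliased. Pre-intervention months remove the first problem, because intervention then varies within cluster. If cluster is the GEE grouping unit, both terms can be estimated, but baseline incidence is absent unless it is added.

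**The case against.** **The model may already use these months.** It is monthly and longitudinal, with calendar time and a time-varying intervention, so October to February could enter as pre-intervention observations. The article does not say whether they do, and silence does not prove omission. Baseline risk also enters through the blocks and the malaria risk covariate. This stands in part: the gap is an unstated use of baseline incidence, and blocking already captures some of the gain.

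**This could be left to the analysis plan.** A full list of adjustments often is. Here, however, the article fixes a covariate list, promises that baseline data will be used in the evaluation, and leaves the two unconnected.

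**The precision figures are soft.** The correlations are assumed. A CV of 0.34 is the total between-cluster value, not the value after blocking. Both points stand, which is why the range is wide and the smaller columns are shown.

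**A stronger reading a reader might infer.** Because the baseline window misses the major peak, a change in incidence could seem biased by season against every intervention. With double weight for April to July, the follow-up year averages 16/12 = 1.33 times the October to February level with no change in malaria. The document does not support this reading. Response is defined against the concurrent LLIN group, which is chosen because incidence varies by season. A seasonal factor common to all arms cancels in that contrast. Nor is the window simply off-season: if October and November are given an assumed weight of 1.5, the ratio is (17/12)/1.2 = 1.18. Either ratio applies only to an uncontrolled before-after comparison, which the Stage 1 intervention section argues against.

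**The official start in March 2020** is not a defect in itself. It coincides with the start of follow-up, and case detection had already begun.

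**Conclusion.** The point holds as a matter of efficiency, not validity. Pre-intervention incidence was being collected, the article promises to use baseline data, and the stated covariates include no baseline value of the primary endpoint. Randomisation, blocking and the LLIN comparator keep the arm comparison unbiased.

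The loss is an avoidable 8% to 54% of between-cluster variance at ICC 0.05 for correlations of 0.3 to 0.8, and about 6% to 44% in the lower-CV cases shown. These figures assume about 47 baseline cases per cluster and early surveillance that was complete and run in the same way in every cluster. The wording that surveillance was first initiated and only later officially started leaves that last assumption open. The correlation may also be weaker for outcomes at month 36 than for the first follow-up year.

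The per-cluster responder sentence is loose about its reference. That is a wording matter, because the comparison with LLIN is stated just before it.

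**What to change.** 1. **Data analysis, if cluster is the GEE grouping unit (preferred).** Say so, and add each cluster's October 2019 to February 2020 log incidence rate as a covariate, with risk block, to the primary and second-aim models.
2. **Data analysis, if cluster is kept as a fixed effect.** Do not add the baseline covariate, which would be aliased. State instead that the October to February months are included as pre-intervention observations. Without them the stage 1 effect cannot be estimated from the stage 1 data.
3. **Stage 1 intervention.** Complete the single-cluster rule so that the reduction is expressed relative to LLIN clusters over identical calendar months, in line with the definition just before it.

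**Cost.** The incidence data for these months come from surveillance already begun, so this is one covariate and a few sentences. The downside is one degree of freedom among 36 clusters, and a noisier baseline if early surveillance was incomplete. Person-time actually observed in those months should be the denominator, and its completeness should be reported by cluster.

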**Methods/design:**

This study will use a longitudinal block-cluster sequential multiple assignment randomized trial (SMART) design with longitudinal outcome measures for a period of 3 years to develop an adaptive intervention for malaria control in western Kenya, the first adaptive trial for malaria control. The primary outcome is clinical malaria incidence rate. This will be a two-stage trial with 36 clusters for the initial trial. At the beginning of stage 1, all clusters will be randomized with equal probability to either LLIN, piperonyl butoxide-treated LLIN (PBO Nets), or LLIN + IRS by block randomization based on their respective malaria risks. Intervention effectiveness will be evaluated with 12 months of follow-up monitoring. At the end of the 12-month follow-up, clusters will be assessed for “response” versus “non-response” to PBO Nets or LLIN + IRS based on the change in clinical malaria incidence rate and a pre-defined threshold value of cost-effectiveness set by the Ministry of Health. At the beginning of stage 2, if an intervention was effective in stage 1, then the intervention will be continued. Non-responders to stage 1 PBO Net treatment will be randomized equally to either PBO Nets + LSM (larval source management) or an intervention determined by an enhanced reinforcement learning method. Similarly, non-responders to stage 1 LLIN + IRS treatment will be randomized equally to either LLIN + IRS + LSM or PBO Nets + IRS. There will be an 18-month evaluation follow-up period for stage 2 interventions. We will monitor indoor and outdoor vector abundance using light traps. Clinical malaria will be monitored through active case surveillance. Cost-effectiveness of the interventions will be assessed using *Q*-learning.

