#### Stage 2 intervention

The stage 2 intervention will be 21 months long, including a 3-month intervention implementation and 18 months of follow-up on the interventions’ impact. The main objective of stage 2 is to identify the optimal adaptive intervention in clusters not responding to the stage 1 intervention, i.e., the non-response clusters at the end of stage 1 will receive a modified intervention to improve the outcome (reduction of malaria incidence) (Fig. 2). In particular, non-responders to stage 1 PBO LLIN treatment will be randomized with equal probability to either PBO LLIN + LSM (larval source management) or an intervention determined by an enhanced reinforcement learning method. Similarly, non-responders to stage 1 LLIN + IRS treatment will be randomized with equal probability to either LLIN + IRS + LSM or PBO LLIN + IRS. Therefore, this design has 4 embedded adaptive interventions (Table 2).

**Table 2 Tab2:** Four embedded adaptive interventions in the proposed SMART trial study

Embedded adaptive intervention	First-stage intervention	Status at end of first-stage treatment	Second-stage intervention option	Subgroup in the design
#1	PBO LLIN	Responder	Continue PBO LLIN	B + C
		Non-responder	PBO LLIN + LSM	
#2	PBO LLIN	Responder	Continue PBO LLIN	B + D
		Non-responder	Enhanced machine learning method	
#3	LLIN + IRS	Responder	Continue IRS	E + F
		Non-responder	LLIN + IRS + LSM	
#4	LLIN + IRS	Responder	Continue IRS	E + G
		Non-responder	PBO LLIN + IRS	

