#### Sample size justification

The primary aim of this study is to determine which initial intervention, PBO LLIN or LLIN + IRS, is more effective in reducing malaria incidence after 36 months. The second aim is to estimate the mean outcomes of the 4 embedded adaptive interventions from months 16 to 36 and to identify the most effective intervention. Sample size calculation is based on the primary aim, using the primary outcome (clinical malaria incidence) and between-group comparison of the average clinical malaria incidence at month 36. The proposed sample size (*n* = 36 clusters) will detect a 10% reduction in clinical malaria incidence with 89.2% power using the current incidence rate in the study sites (302 clinic cases per 1000 person-years) and a 2-tailed *α* = 0.05 with a human population size of 500 per cluster (Table 3). If malaria incidence is 30% lower than the current value, the design will still detect a 20% incidence reduction with 97% power (Table 3). This calculation assumes a 1:1 response/non-response ratio, a fixed cluster size of 500 participants, and an intra-cluster correlation coefficient of 0.05 [89]. This sample size is likely powered to detect smaller changes in incidence reduction, as previous studies in Kenya and Ghana indicated intra-cluster correlation coefficients of < 0.02 [90].

**Table 3 Tab3:** Power calculation (%) for proposed cluster-randomized SMART trial. Shown are degrees of power to detect four levels of incidence reduction under three incidence scenarios

Annual incidence rate (cases/1000 population)	Reduction in malaria incidence			
	40%	30%	20%	10%
Observed in the site: 302	> 99.9	> 99.9	> 99.9	89.2
30% lower value: 211	> 99.9	99.8	97.0	59.0
30% higher value: 393	> 99.9	> 99.9	> 99.9	97.0

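### The stated follow-up dates (March 2020 to February 2022, 24 months) do not fit the 36-month design or its month-36 primary comparison

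*Protocol article*

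**What the plan says.** The design sections of the protocol article agree with one another on 36 months.

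- The abstract (Methods/design) plans "longitudinal outcome measures for a period of 3 years".
- Stage 1 intervention: "Stage 1 (initial intervention) will be 15 months long, including a 3-month field implementation of interventions and 12 months of follow-up".
- Stage 2 intervention: "The stage 2 intervention will be 21 months long, including a 3-month intervention implementation and 18 months of follow-up".
- Sample size justification: the primary aim is to find "which initial intervention, PBO LLIN or LLIN + IRS, is more effective in reducing malaria incidence after 36 months", and power is based on a "between-group comparison of the average clinical malaria incidence at month 36". The second aim covers months 16 to 36.

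The Trial status section supplies the calendar: "The stage 1 intervention started recruiting in late February 2020, and recruitment will continue until March 2021 as anticipated". It continues: "Post-intervention follow-ups started in March 2020 till February 2022". It also reports that cohort case surveillance was initiated in October 2019 and officially started in March 2020.

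The text shown mentions no extension and does not explain the difference. The schedule in Table 1 and the design diagram in Fig. 2 are not reproduced in the text available, so they could not be checked.

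**The concern.** The only end date given for follow-up falls well before the time point on which the primary aim and the power calculation rest. A reader who follows that date finds no month-36 incidence to compare and a second-aim window cut short at its late end. That window is where the four embedded adaptive interventions are estimated and compared.

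The start date also conflicts. The Stage 1 section places three months of field implementation before the 12 months of follow-up. The Trial status section has post-intervention follow-up beginning in March 2020, within weeks of the stage 1 start and so inside that implementation period. Response status at the end of the 12 months decides which clusters are re-randomized, so the boundaries of that window need to be unambiguous.

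**Working it through.** **Inputs.** Stage lengths come from the Stage 1 and Stage 2 intervention sections, the month-36 and months 16–36 targets from Sample size justification, and the calendar dates from Trial status.

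**Design length reproduced.** Stage 1: 3 + 12 = 15 months. Stage 2: 3 + 18 = 21 months. Total: 15 + 21 = 36 months, which matches the stated primary time point.

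**Stated follow-up span.** March 2020 to February 2022 inclusive = 24 months.

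**Additive timetable from the stated start** (late February 2020, so month 1 = March 2020):

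- Stage 1, months 1–15: March 2020 to May 2021.
- Stage 2 implementation, months 16–18: June to August 2021.
- Stage 2 follow-up, months 19–36: September 2021 to February 2023.
- February 2022 is month 24, so the shortfall is 36 − 24 = 12 months.
- Stage 2 follow-up observed by then: September 2021 to February 2022 = 6 of 18 months.
- Months 16–36 observed: months 16 to 24 = 9 of 21.

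**Sensitivity to the start of month 1:**

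| Month 1 taken as | Month 36 falls in | February 2022 is month | Short by | Stage 2 follow-up observed | Months 16–36 observed |
|---|---|---|---|---|---|
| March 2020 | February 2023 | 24 | 12 | 6 of 18 | 9 of 21 |
| February 2020 | January 2023 | 25 | 11 | 7 of 18 | 10 of 21 |
| December 2019 (March 2020 = month 4, just after implementation) | November 2022 | 27 | 9 | 9 of 18 | 12 of 21 |
| October 2019 (case surveillance initiated) | September 2022 | 29 | 7 | 11 of 18 | 14 of 21 |
| July 2019 (baseline surveys) | June 2022 | 32 | 4 | 14 of 18 | 17 of 21 |

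The last three rows are deliberately lenient: they start the clock before the stage 1 start that the article states.

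**Implementation overlapping follow-up.** Suppose the 12-month stage 1 follow-up is March 2020 to February 2021.

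- With a 3-month stage 2 implementation in March to May 2021, stage 2 follow-up from June 2021 to February 2022 gives 9 of 18 months.
- If stage 2 implementation also overlaps follow-up, March 2021 to February 2022 gives 12 of 18 months.
- With no implementation time at all, the planned follow-up is 12 + 18 = 30 months. From March 2020 that ends in August 2022, 6 months after the stated end.

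**The case against.** The strongest reply is that four design statements agree on 36 months and the outlier is one loosely worded sentence in an administrative paragraph. It may be a slip, or it may describe only part of the follow-up. Nothing in Trial status says that the cohort closes at month 24 or that stage 2 is shortened. This stands, and it limits the point to a contradiction between stated dates. A reader might infer that the month-36 data will never be collected; the article does not show that.

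Two further inferences are tempting.

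- *Most of stage 2 follow-up is lost, and with it the main transmission season.* This needs both a true end in February 2022 and the additive timetable. The remaining 6 months would then hold the October–November minor peak and none of the April–June major peak described under Study area and cluster selection. On the overlapping readings 9 to 12 of 18 months remain, and the observed period includes June 2021 or the whole of April–June 2021.
- *Implementation months are analysed as exposed, diluting stage 1 effects and distorting response classification.* The Stage 1 section separates implementation from the 12-month follow-up. Trial status reports when follow-up ran, not which months enter the outcome, and case surveillance was initiated before any intervention. Data analysis models monthly incidence with intervention as a time-varying covariate; the coding of transition months can be left to an analysis plan that is not shown.

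The reply does not reconcile the dates. No start date in the article, and no treatment of the implementation periods, brings month 36 or even 30 months of pure follow-up inside February 2022.

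**Conclusion.** The contradiction holds. The article states 24 months of post-intervention follow-up for a design that needs 36. The gap is 12 months on the stated start and at least 4 months on the most lenient start date given.

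The consequences are conditional on February 2022 being the real end. The primary time point would then not be observed, and the second-aim window would be truncated. How much of stage 2 follow-up survives depends on the timetable: about 6 of 18 months if the stages are added from the stated start, 9 to 12 of 18 if implementation overlaps follow-up.

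The March 2020 follow-up start and the preceding 3-month implementation also need reconciling. That is a conflict of wording; no analysis error is shown.

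The main assumption is that month 1 is March 2020, taken from the late-February 2020 start. The unseen Table 1 could show which date is intended, but it would not remove the conflict in the text. The point matters because the primary aim and the sample-size basis both depend on a month that the stated dates exclude.

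**What to change.** Reconcile the article to a single timetable.

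1. If the 36-month design stands, correct the end of follow-up in Trial status to month 36, about February 2023 on the stated start. This costs one line.
2. If February 2022 is the real end, restate the primary time point, the months 16–36 window and the sample-size basis to the months actually observed. This changes the primary comparison, so it should be documented as an amendment.
3. In either case, state that the 12-month stage 1 outcome window follows the implementation period set out in the Stage 1 section, give its calendar dates, and use the same calendar window in all arms, including LLIN. Clarify whether the March 2020 date marks the start of surveillance or the start of that window. This is a wording change only, provided the analysis already follows the Stage 1 section.
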